#### Participant timeline {13}

Timeline is presented in Figs. 1 and 2.

**Fig. 1 Fig1:**
[figure not shown]
Flow chart for inclusion of patients in SOULMATE

**Fig. 2 Fig2:**
[figure not shown]
Protocol for study visits after inclusion in the SOULMATE trial

#### Sample size {14}

It is expected that the percentage of subjects who will reach the endpoint of overall survival after 5 years will be 55% in the study group and 10% in the control group. Based on this assumption, with 80% power for the superiority comparison (Fisher’s exact test) of the primary endpoint between the two treatment groups, and a 2-sided type 1 error of 5%, allowing for a 20% drop-out rate in the LT-group, we plan to randomize 45 subjects to the two treatment groups in a 5:4 ratio (LT:BET).

#### Recruitment {15}

Information about the study and the possibility to enroll patients will be communicated on national meetings with attending oncologists as well as colorectal and liver surgeons. Information has been communicated to the Swedish Colorectal Patients Associations and through the National Swedish Medical Journal. An enrolment time of 60 months is expected.

### Assignment of interventions: allocation

#### Sequence generation {16a}

The patients will be enrolled by the physicians at respective sites when the subjects have been accepted by the National Liver Surgery Conference. The randomization procedure will be computer-generated through the electronic case report formula (MediCase eCRF), and it is not possible for physicians to predict the outcome of the randomization. Stratification will be performed per included site; the limited size of the study allowed for no other stratification factors.

#### Concealment mechanism {16b}

Randomization is done by the eCRF only and concealed from physicians until the intervention is allocated.

#### Implementation {16c}

After the subjects have been assigned to the study or control group through the randomization procedure, they be informed by their treating physician. Patients subjected to the study group will then be referred to one of the two transplant center for pre-operative work-up.

### Assignment of interventions: blinding

#### Who will be blinded {17a}

The SOULMATE trial is an open trial, and no blinding will be used in any part of the study procedures.

#### Procedure for unblinding if needed {17b}

The design of the SOULMATE trial is open label, so unblinding will not occur.

### Data collection and management

#### Plans for assessment and collection of outcomes {18a}

The patients will be followed for five years. Study visits will be performed at each center at baseline and every third month the first 3 years and every sixth month hereafter. Follow-up will include the following mandatory tests: MRI or CT of the liver and CT of the thorax, blood samples, including tumor-markers and plasma samples for liquid biopsies. European Quality of Life Five Dimension Three Level Scale (EQ5D-3L) quality of life questionnaire will be answered at every visit, and EORTC QLQ-C30 and QLQ- LMC21 will be filled in at baseline and at 3, 6, 12, 18, 24, 36, and 60 months.

The timeline is to be found in an electronic clinical report form (e-CRF).

#### Plans to promote participant retention and complete follow-up {18b}

All study subjects, except those that withdraw consent for the study, will be followed for the study period. Patients that discontinue their follow-up visits, without withdrawing consent, will be followed for survival.

#### Data management {19}

The designated site staff will enter the data required by the protocol into the e-case report forms (eCRF). The principal investigator at each participating site is responsible for assuring that data entered into the eCRF is complete, accurate, and that entry is performed in a timely manner. The signature of the investigator will attest the accuracy of the data on each eCRF. If any assessments are omitted, the reason for such omissions will be noted on the eCRFs. Corrections, with the reason for the corrections, will also be recorded/tracked in the eCRF. All data management activities will be completed prior to final closure of the database. All original research data will be managed and stored according to Swedish law.

#### Confidentiality {27}

All patient data collected and processed for the purposes of this study will be managed by the sponsor with adequate precautions to ensure the confidentiality of those data, and in accordance with applicable national and national laws and regulations on personal data protection. No patient-identifiable data will be obtained. In any presentations of the results of this study, at meetings or in publications, the patients’ identity will remain confidential. In all activities, the GDPR (General Data Protection Regulation) will be followed to ensure protection of sensitive personal information, and the study will perform in accordance with WHO guidelines for good clinical practice (GCP).

#### Plans for collection, laboratory evaluation, and storage of biological specimens for genetic or molecular analysis in this trial/future use {33***}***

Plasma samples will be collected during the study period at every study related visit. In patients randomized to liver transplantation, tissue from metastases as well as macroscopically normal liver will be sampled. After preparation and aliquoting, both the plasma and the tissue samples will be stored in – 70 °C, in a preexisting biobank at the Sahlgrenska University Hospital.

### Statistical methods

#### Statistical methods for primary and secondary outcomes {20a}

The Transplant Institute, Gothenburg, will be responsible for all statistical programming and analysis, as well as quality control and validation of programming and statistical analysis. The responsible biostatistician will coordinate the statistical analysis. A detailed description of all the statistical analyses of all efficacy and safety variables together with an overview of tables and figures will be given in a separate statistical analysis plan (SAP). The SAP has been finalized before the database of the study is locked. Any deviations from the SAP will be justified in the clinical study report.

The primary analysis of efficacy data will be based on the intention-to-treat (ITT) population, defined in the SAP. Patients will be analyzed according to their randomized treatment.

#### Interim analyses {21b}

A data monitoring committee (DMC) will be appointed. The DMC will perform an interim analysis after 40% of the subjects in the study have been followed for 2 years. The sponsor has the right to terminate or change the trial prematurely if there are any relevant medical or ethical concerns or if completing the trial is no longer feasible. If such action is taken, the reasons for terminating the trial must be documented in detail. Premature termination of the trial will be considered if:The risk-benefit balance for the trial subjects changes markedlyThe sponsor considers that the trial must be discontinued for safety reasonsAn interim analysis or results of other research show that one of the trials treatments arms are superior or inferior to another

Inclusion in the study will be temporarily stopped if two post-operative deaths within 90 days of liver transplantation occurs. The causes of death will then be analyzed in detail and discussed within the data monitoring committee (DMC) before any final decision about continuing or stopping the trial.

In the case of a prematurely stopped trial, the patients will be taken care of and followed at the discretion of the treating physician.

If, during the conduct of the study, new publications clearly shows that liver transplantation is beneficial for the study population, the study protocol will be amended so that all consecutively included patients are assigned to the transplantation arm.

#### Methods for additional analyses (e.g., subgroup analyses) {20b}

In the liver transplantation group the overall survival after 2 and 5 years from randomization will be analyzed in the following subgroups:Subjects transplanted with a liver from a donor with a history of malignancy will be compared to subjects transplanted with a liver from a donor with no history of malignancySubjects transplanted with a liver from a donor previously tested positive for virus (hepatitis or HIV) compared to subjects transplanted with a liver from a donor without positivity for virusSubjects that have experienced an extrahepatic recurrence will be compared with subjects that has experienced an intrahepatic recurrenceSubjects that have undergone surgical or ablative treatment for recurrence will be compared to subjects that have not undergone any surgical or ablative treatment for recurrence

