The procedure to resect all metastases, even those which are deemed to be unresectable, by total hepatectomy, followed by liver transplantation (LT), is already performed for other malignant indications, such as hepatocellular carcinoma (HCC), highly selected perihilar cholangiocarcinoma (CCC), and more recently for patients with very-early stage intrahepatic CCC. LT has also been performed for selected patients with liver metastases from neuroendocrine tumors [22–24]. In the beginning of the transplantation era, LT for unresectable CRLM was thought as a method for potential cure. According to the European Liver Transplant Registry, 58 patients underwent liver transplantation for unresectable CRLM 1977-1995 with a 5-year OS of 18%, and a graft loss of 44%, despite no signs of tumor recurrence [25].

In Vienna, a small series of LT for CRLM was performed between 1982 and 1994. Five year OS was reported as low as 12% with a 30-day mortality rate of 30% [26]. After these dismal results, unresectable CRLM was considered as a contraindication for LT. However, the fact that there were no standardized criteria for patient selection, no standardized immunosuppression protocols, and limited experience in the surgical and anesthesiologic procedure of LT might have contributed to the unsatisfactory results.

In 2006, the SECA-I study was opened at Oslo University Hospital. It was a groundbreaking prospective, non-randomized pilot study of LT for isolated nonresectable CLRM. The new protocol was possible to implement, since availability of liver grafts in Norway during the study period was sufficient. In the SECA-I study; 25 patients were included, of which four patients were dropouts due to extrahepatic disease. Finally, 21 patients underwent LT. All patients had undergone previous R0 resection for the primary CRC, no signs of extrahepatic disease, and had received at least 6 weeks of chemotherapy. The SECA-I study showed a 5-year OS of approximately 60%, even though there was recurrence of the CRC in 90% of the patients [27].

The main site of recurrence was in the lungs, but the lung metastases seemed to be slow-growing despite post-transplantation immunosuppression and did not significantly affect survival [28]. Compared to a similar matched cohort of isolated CRLM included in the first-line NORDIC-VII trial in which the efficacy of cetuximab in combination with fluorouracil/folinic acid and oxaliplatin was investigated, LT showed a significant increased OS [29].

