#### Intervention description {11a}

##### Arm A: liver transplantation (LT) + best established treatment (BET)

Patients subject to LT will, during the waiting time, receive individualized oncological therapy, with the aim to keep the disease stable but at the same time minimize side effects that could compromise transplantation.

If possible, patients randomized to LT should be transplanted within 12 weeks after randomization, although due to shortage of organs, waiting time might be longer. Hence, there is no upper time limit on the waiting list, if the patient fulfills the study criteria. The surgical procedure is performed as a standard liver transplantation.

The study patients included in the experimental arm will be added to the regular waiting list for LT. We will evaluate the use of livers from extended criteria donors to decrease the risk of prolonging waiting time for patients with already accepted indications for LT. While patients included in this study will have basically normal liver function with a normal MELD-score and no portal hypertension, the SOULMATE patients will probably be more able to tolerate an extended criteria liver graft, than patients with more suppressed liver function.

Examples of extended criteria donors are donors of higher age and/or higher grade of comorbidity, such as obesity/liver steatosis and donors with a risk of transmission of infectious or malignant disease.

The guide to the quality and safety of organs for transplantation (EDQM 2016, 29) will be used. Donors with a high risk for transmission of malignancy can be accepted by the transplant surgeon after consideration in individual cases, but donors with an unacceptable risk for transmission defined according to EDQM (29) will not be accepted.

In case of an early technical complication or delayed graft function in a study patient, with a need for an early re-transplantation, a kind request for a liver could be applied as for other liver transplanted patients. If such a complication occurs in the study, a thorough analysis of the causes is mandatory.

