#### Methods in analysis to handle protocol non-adherence and any statistical methods to handle missing data {20c}

The data will be analyzed both for intention to treat and per protocol. In the intention-to-treat analysis, all subjects will be analyzed according to the arm they have ben randomized to. Patients in arm A, which have been assigned to liver transplantation, will be analyzed in this group even if they for any reason had not undergone liver transplantation. In the per-protocol analysis; the subgroup of patients that have been assigned to liver transplantation but not undergone transplantation will be excluded from the analysis.

Since all patients will be under continuously supervision by treating medical staff, most frequently oncologist, the risk of missing follow-up is considered low. For the primary outcome, survival, the amount of missing data is expected to be small. For parameters with a higher proportion of missing outcomes per group, the characteristics of participants for whom no outcomes were observed, and the reasons for missing outcome data will be reported.

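### The planned LT-arm comparison of patients treated v not treated for recurrence counts survival from randomisation, so immortal time and an undefined reference group leave its result uninterpretable

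*Protocol article*

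**What the plan says.** The section Methods for additional analyses {20b} fixes one outcome and time origin for four LT-arm comparisons: "the overall survival after 2 and 5 years from randomization will be analyzed in the following subgroups". Two of the four split patients by donor characteristics. The other two split them by what happens after randomisation:

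- Site of recurrence: subjects that "have experienced an extrahepatic recurrence will be compared with subjects that has experienced an intrahepatic" recurrence.
- Treatment of recurrence: subjects that "have undergone surgical or ablative treatment for recurrence will be compared to subjects that have not undergone any surgical or ablative treatment" for recurrence.

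The section states no landmark, no time-dependent handling and no restart of the clock at recurrence, and it does not limit the untreated group to patients with a recurrence. Two other passages bear on who sits in that group. Under Arm A, on waiting for a graft: "Hence, there is no upper time limit on the waiting list, if the patient fulfills the study criteria". Under the handling of non-adherence {20c}, patients assigned to LT "will be analyzed in this group even if they for any reason had not undergone liver transplantation".

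**The concern.** To be counted as treated for recurrence, a patient must live through the wait for a graft, the transplantation, the time to recurrence and the interval to surgery or ablation. A patient who dies during any of these is untreated by construction. With the clock started at randomisation, all of that guaranteed survival is credited to treatment.

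The reference group has a second problem. Taken literally it is everyone in the LT arm without such treatment, including patients who never recurred and, on an intention-to-treat reading, patients never transplanted. Patients free of recurrence tend to do well and raise survival in the reference group. The two errors act in opposite directions, so the net error cannot be predicted.

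Recurrence will probably be common. The background describes an earlier LT series with about 60% 5-year OS, "even though there was recurrence of the CRC in 90% of the patients". Readers will look at this comparison, and a difference in either direction could arise from the grouping alone.

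**Working it through.** **Inputs from the article.** The groups and time origin are as above. LT-arm size is 45 × 5/9 = 25. Planned 5-year OS in the LT arm is 55%. The article gives no figure for these subgroup analyses, so there is none to reproduce.

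**Assumed inputs (not in the article).** Recurrence hazard λ = 0.7 per year among patients prone to recur; a share π never prone; death hazard after recurrence h = 0.2 or 0.3 per year; half of recurrences selected for treatment; exponential delay to treatment with mean d = 0.25 or 0.5 years; no deaths before recurrence; **no effect of treatment**. A patient counts as treated if alive at the treatment date and treated within 5 years.

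**Step 1, by hand.** With δ = 1/d, a selected patient survives to treatment with probability δ/(δ + h). For d = 0.5 and h = 0.3 this is 2/2.3 = 0.87, so 13% of those selected die first and are counted as untreated. Ignoring the 5-year limit, mean survival after recurrence is:

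- all recurred: 1/h = 3.33 years
- treated: 1/(δ + h) + 1/h = 0.43 + 3.33 = 3.77 years
- untreated: (3.33 − 0.435 × 3.77)/(1 − 0.435) = 3.00 years, where 0.435 = 0.5 × 0.87 is the treated share

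The gap is about 0.77 years although treatment does nothing.

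**Step 2, OS from randomisation, recurred patients only (simulated).**

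| h | d | 2 years, treated v untreated | gap | 5 years, treated v untreated | gap |
|---|---|---|---|---|---|
| 0.2 | 0.25 | 86.2% v 81.0% | 5.2 | 50.9% v 46.9% | 4.0 |
| 0.2 | 0.5 | 88.3% v 79.6% | 8.7 | 52.8% v 45.5% | 7.3 |
| 0.3 | 0.25 | 80.5% v 73.8% | 6.7 | 37.0% v 32.9% | 4.1 |
| 0.3 | 0.5 | 83.2% v 72.1% | 11.1 | 39.0% v 31.7% | 7.3 |

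A variant that allows deaths before recurrence (median time to recurrence 0.8 years, median survival after it 3.5 years, d = 0.5, about 92% recurring) gives 85.5% v 75.2% and 47.5% v 39.7%, gaps of 10.3 and 7.8 points. The range is therefore about 5 to 11 points at 2 years and 4 to 8 at 5 years.

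**Step 3, all untreated patients as reference.** Let w be the share of the untreated group without a recurrence by 5 years; all of these are alive in this model. Reference 5-year OS is w × 100% + (1 − w) × OS of untreated recurred patients. Overall 5-year OS is π + (1 − π)(λe^(−5h) − he^(−5λ))/(λ − h).

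| π | h | d | overall 5-year OS | w | treated v all untreated, 5 years | difference |
|---|---|---|---|---|---|---|
| 0 | 0.2 | 0.5 | 50.3% | 5.3% | 52.8% v 48.4% | +4.4 |
| 0 | 0.3 | 0.5 | 36.8% | 5.2% | 39.0% v 35.2% | +3.8 |
| 9.5% | 0.2 | 0.5 | 55.0% | 20.2% | 52.8% v 56.5% | −3.7 |
| 28.5% | 0.3 | 0.25 | 54.8% | 45.1% | 37.0% v 63.2% | −26.2 |

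Last row: 0.285 + 0.715 × 0.368 = 0.548 overall, and 0.451 × 100 + 0.549 × 32.9 = 63.2. The last two rows match the planned 55%, and in both the sign has reversed.

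**Step 4, does the remedy work?** Restricting to recurred patients, starting at recurrence and letting treatment vary over time gives a death-rate ratio of 0.99 to 1.01, against a truth of 1.0. This was run over median times to recurrence of 0.8 to 1.5 years, median survival after recurrence of 2 to 3.5 years and mean delays of 0.25 to 1 year. The uncorrected ratio among recurred patients over the same scenarios is 0.68 to 0.88.

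**Step 5, site of recurrence.** With equal death hazards after recurrence (median survival 3.5 years) and equal timing at the two sites, 5-year OS is 49.2% v 49.2%. With median times to recurrence of 0.75 v 1.5 years it is 46.4% v 52.9%. Counted from recurrence, 2-year survival is 67% in both groups.

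**The case against.** **The analysis plan may settle it.** The article sends detailed methods to a separate plan that is not shown, and estimators, landmarks and a descriptive label are ordinary content for it. That stands for those details. It does not cover the time origin and the groups, which the article itself fixes and which conflict with each other.

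**The untreated group may mean recurred but untreated.** This is a fair reading, since the preceding item concerns patients with recurrence. The text does not say so, and the narrower reading removes only the mixing; the gaps in step 2 remain.

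**The practical effect is small.** These are additional analyses, absent from the stated objectives, with no hypothesis or alpha attached. With, say, 10 treated and 12 untreated patients, the standard error of the 5-year difference is about √(0.39 × 0.61/10 + 0.32 × 0.68/12) = 0.20. That keeps the grade low. Imprecision does not remove bias.

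**Stronger readings that the article does not support.** A reader might infer that both recurrence-based comparisons carry built-in immortal-time bias and both mix in patients who never recurred. In the site comparison everyone has survived to a recurrence, so no such patient enters and bias needs different timing at the two sites. A reader might also take one simulated gap as the size of the error. With π = 0 and h = 0.3 overall 5-year OS is 37%, well below the planned 55%, so only a range is defensible. Finally, the article does not say that the result will be presented as evidence for treating recurrence.

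**Conclusion.** The point holds for the comparison by treatment of recurrence. As written, it favours treatment through immortal time whatever the true effect, and on the literal wording it also dilutes the reference group with patients who never recurred. The ranges in steps 2 and 3 rest on assumed hazards, delays and selection; they show the order of magnitude and the unstable sign, and do not predict this trial's result.

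For extrahepatic v intrahepatic recurrence the concern is conditional on timing. There is also a gap in definition, because a patient with both sites has no assigned group.

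The primary intention-to-treat comparison of 5-year OS groups patients as randomised and is untouched. The correction is minor to moderate.

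**What to change.** In the section on additional analyses {20b}, and in the analysis plan:

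1. **Treatment of recurrence.** Restrict the comparison to LT-arm patients with a recurrence. Count survival from first recurrence. Enter surgical or ablative treatment as a time-dependent covariate, or use a fixed landmark after recurrence that classifies patients by treatment received up to then.
2. **Site of recurrence.** Count survival from first recurrence, and use three exclusive classes at first recurrence: liver only, extrahepatic only, both.
3. **Status.** Label both comparisons descriptive. Even with correct timing, patients selected for local treatment differ from those who are not, and about 25 patients cannot support adjustment.

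The cost is a wording change. Dates of recurrence and of treatment are needed; the scheduled liver and thorax imaging already supports the first. No change to sample size, visits or patient care follows.

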#### Methods in analysis to handle protocol non-adherence and any statistical methods to handle missing data {20c}

The data will be analyzed both for intention to treat and per protocol. In the intention-to-treat analysis, all subjects will be analyzed according to the arm they have ben randomized to. Patients in arm A, which have been assigned to liver transplantation, will be analyzed in this group even if they for any reason had not undergone liver transplantation. In the per-protocol analysis; the subgroup of patients that have been assigned to liver transplantation but not undergone transplantation will be excluded from the analysis.

Since all patients will be under continuously supervision by treating medical staff, most frequently oncologist, the risk of missing follow-up is considered low. For the primary outcome, survival, the amount of missing data is expected to be small. For parameters with a higher proportion of missing outcomes per group, the characteristics of participants for whom no outcomes were observed, and the reasons for missing outcome data will be reported.

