### Objectives {7}

The aim of this randomized study is to evaluate if liver transplantation in addition to best established treatment (BET) will extend OS for patients with CRLM not suitable for operation or ablation, compared to BET only. Secondary objectives include 2-year OS, median OS, and progression-free survival (PFS). Differences between the two groups regarding quality of life will be evaluated as well as health economic perspectives and the utility of biomarkers. Eventual risks by utilizing a broader donation pool will also be evaluated.

Primary objective:Five-year overall survival from randomization

Secondary objectives:Two-year overall survival from randomizationMedian overall survivalProgression-free survivalHepatic progression-free survivalExtrahepatic recurrence-free survivalQuality of lifeHealth economic evaluationRate of primary non-function liver graftsRate of donor-derived malignancies

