#### Criteria for discontinuing or modifying allocated interventions {11b}

If a patient during the waiting time in arm A has extrahepatic progression, proceeding to LT is not allowed. If a patient progress only within the liver, it is possible to stay on the waiting list for LT, until the patient is proclaimed technically not transplantable by the liver transplant team.

Patients may be discontinued from the study at any time if, in the opinion of the investigator, it is medically necessary or if it is the expressed wish of the patient. Patients are free to discontinue their participation in the trial at any time.

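### The supplementary per-protocol analysis drops untransplanted patients from the LT arm only, so it favours LT even with no effect; the primary ITT analysis is unaffected

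*Protocol article*

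**What the plan says.** Section {20c} of the protocol article plans two analyses: "The data will be analyzed both for intention to treat and per protocol". Its only rule for the per-protocol set concerns arm A: "the subgroup of patients that have been assigned to liver transplantation but not undergone transplantation will be excluded from the analysis". It states no exclusion for arm B.

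Section {20a} fixes the hierarchy: "The primary analysis of efficacy data will be based on the intention-to-treat (ITT) population". Section {20c} adds that arm A patients stay in their arm for ITT whether or not they are transplanted.

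Two other sections determine who goes untransplanted and when.

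- Section {11b}: "If a patient during the waiting time in arm A has extrahepatic progression, proceeding to LT is not allowed". A patient with progression confined to the liver may stay listed, but only "until the patient is proclaimed technically not transplantable by the liver transplant team". The same section lets patients or investigators end participation.
- The description of arm A: if possible, "patients randomized to LT should be transplanted within 12 weeks after randomization", but "there is no upper time limit on the waiting list".

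The primary objective is "Five-year overall survival from randomization", so the survival clock starts before the wait. Two-year and median overall survival are secondary objectives. The description of arm B bars cross-over to arm A.

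**The concern.** The exclusion depends on what happens after randomization, applies to one arm, and is tied to prognosis by the protocol's own rules. Two mechanisms follow, and both act in the same direction.

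1. **Selection.** Patients who progress outside the liver, or within it until a transplant is no longer technically possible, leave the LT arm of the per-protocol set. Comparable BET patients are kept.
2. **Guaranteed survival time.** Every LT patient in the set must have lived from randomization to transplant, an interval without an upper limit. BET patients who die in that interval still count.

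At stake is a supplementary estimate that appears to describe the benefit of transplantation but is partly produced by the choice of patients. This matters most for two-year and median survival, where early deaths weigh heavily.

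**Working it through.** **Inputs from the protocol article.** Section {14} gives five-year survival of 55% (LT) and 10% (BET), Fisher's exact test, two-sided 5%, 80% power, 20% drop-out in the LT arm, and 45 patients at 5:4, that is 25 LT and 20 BET. The Trial design section prints the drop-out as 208%; only 20% reproduces the total.

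**The plan's own figure.** The continuity-corrected two-proportion formula for 55% against 10% gives 20 per arm. Inflating the LT arm gives 20/(1 − 0.20) = 25, and 25 + 20 = 45. Exact Fisher power at 20 v 20 is 83.9%. The stated size is reproduced.

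**Bias on the primary endpoint with no LT effect.** Let S be five-year survival in both arms, d the share of arm A not transplanted, and q the five-year survival of that share. Per-protocol survival in the LT arm is then

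(S − d·q)/(1 − d).

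With S = 10% and d = 20%:

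| q (assumed) | Per-protocol LT | BET | Bias |
|---|---|---|---|
| 0% | 0.10/0.80 = 12.5% | 10% | +2.5 points |
| 5% | (0.10 − 0.01)/0.80 = 11.25% | 10% | +1.25 points |
| 10% | (0.10 − 0.02)/0.80 = 10% | 10% | 0 |

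By enumeration, Fisher's test favours LT significantly in 1.4% of trials at q = 0 (20 v 20). The rate is 0.6% in a set of that size without selection, and 0.5% under ITT (25 v 20). Selection roughly doubles the rate, but it stays below 2.5%.

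**Guaranteed survival time alone.** Assume a constant hazard with 10% alive at five years. Conditional on being alive at the time of transplant:

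| Wait | 5-year survival | Median, months from randomization |
|---|---|---|
| none required | 10% | 18.1 |
| 12 weeks (protocol target) | 11.1% | 20.8 |
| 6 months (assumed) | 12.6% | 24.1 |
| 12 months (assumed) | 15.8% | 30.1 |

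**Secondary endpoints with no LT effect.** These results come from simulation: 25 v 20, exponential survival, 10% at five years in both arms. The 5 of 25 LT patients (20%) with the lowest value of a score correlated with survival are excluded. The log-rank test, censored at five years, is an assumption; the protocol article does not name it.

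| Correlation (assumed) | LT 2-year OS (BET 40%) | LT median, years (BET 1.5) | Log-rank favours LT |
|---|---|---|---|
| 0.3 | about 43% | about 1.7 | about 5% |
| 0.5 | 46% | 1.8 | about 7% |
| 0.8 | 49% | 2.0 | 10-11% |
| 1.0 | 50% | 2.0 | about 12% |

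At correlation 0 the log-rank rate is about 2.5%, and under ITT it is about 3%, so selection produces the excess. The last row can be checked by hand. Removing the shortest-lived 20% gives two-year survival of 0.398/0.8 = 50%. The new median is where S(t) = 0.4, at 1.99 years against 1.51.

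**Check of the proposed estimator.** If 80% are transplanted with 55% survival and 20% are not, with 10%, ITT survival in the LT arm is 0.8 × 0.55 + 0.2 × 0.10 = 46%. CACE = (0.46 − 0.10)/0.8 = 0.45, which recovers the planned difference of 55% − 10%.

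**The case against.** The strongest reply is that nothing confirmatory depends on this set. ITT is primary, and the protocol states plainly that untransplanted arm A patients remain in it. On the primary endpoint, with the only test the article names, the bias is at most 2.5 points beside a planned difference of 45 points, and the error rate stays under nominal. All of this stands.

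The mix of reasons for going without a transplant is also unknown. Some patients will withdraw for reasons unrelated to prognosis, patients with liver-only progression may stay listed, and a 12-week wait moves five-year survival only to 11.1%. This stands too. It is why the secondary figures are given as a range down to a correlation of 0.3, where the excess is modest.

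A reader might infer that the per-protocol result could displace an inconclusive ITT result as the trial's message. If the 20% who drop out stay in ITT with 10% survival, Fisher power at 25 v 20 is 73.1%, not 80%. That is a separate sample-size matter, and nothing in the document promotes the per-protocol result over ITT.

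A reader might also infer a seriously inflated false-positive rate on the primary endpoint. With the protocol's own 10% and 20%, that does not occur. Larger Fisher rates arise only under figures the protocol does not give: 3.8% with 40% untransplanted, and 17% if baseline survival is also 30%.

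The unseen SAP may define the set further, but the article already fixes this exclusion, so the point does not rest on something left to the SAP.

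**Conclusion.** The point holds as a defect in a supplementary analysis. The per-protocol rule is one-sided and linked to prognosis, and its bias runs towards LT. It vanishes only if the excluded patients would have survived as well as the rest.

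For five-year survival it is small: at most 12.5% against 10%, with Fisher's test favouring LT about 1.4% of the time. For the secondary endpoints it is material: two-year survival about 43-50% against 40%, median about 1.7-2.0 against 1.5 years, and an assumed log-rank test favouring LT in about 5-12% of trials.

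The 20% untransplanted is the protocol's drop-out allowance, read here as non-transplantation. The constant hazard, the correlations of 0.3 to 1.0 and the log-rank test are assumptions. The primary ITT conclusion is not threatened. The change should be made because the direction of the bias is known in advance and the remedy is cheap.

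**What to change.** Replace the one-sided exclusion with a CACE: the ITT difference in five-year survival divided by the proportion of arm A transplanted, with a bootstrap or delta-method confidence interval, labelled supplementary. Because cross-over to arm A is barred, non-adherence is one-sided and this simple ratio applies.

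If a per-protocol set is kept, define it by one landmark rule applied to both arms (alive and free of extrahepatic progression at a fixed time), in place of the transplantation condition, and label it non-confirmatory.

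A Cox model with transplantation as a time-dependent covariate should not be relied on as the remedy. It corrects guaranteed survival time, but waiting-list progressors would count as untransplanted follow-up, so the selection remains.

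The cost is wording in the protocol and SAP; sample size, data collection and clinical rules do not change. The main limitation is that CACE assumes assignment to LT without transplantation does not itself alter survival. Section {11d} allows chemotherapy to be modified on the waiting list, so that assumption should be stated with the result.
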